#### Exclusion criteria

Known or suspected serious spinal pathology (e.g. metastatic disease of spine)Confirmed fracture or dislocation at time of injury (WAD IV)WAD III (neurological compromise, e.g. decreased reflexes, muscle power)Previous whiplash injury or neck pain condition requiring treatmentPatients using gabapentin/pregabalinPatients with known peripheral neuropathyKnown hypersensitivity to pregabalin use (hives, blisters, rash, dyspnea and wheezing)History of renal insufficiencyWomen who are pregnant or breastfeedingHistory of psychiatric illness or substance abusePatient Health Questionnaire (PHQ-2) of 3 or more [35]Inability to speak and write in English

### Recruitment and procedure

Recruitment will be from EDs of public hospitals in Queensland, Australia. Research staff will regularly check the Emergency Department Information System (EDIS) and identify any potentially eligible patients. They will liaise with an ED doctor to ensure the patient’s history and screening results are clear for study commencement. Eligible participants who present at ED when research staff are present will complete informed consent documentation after discussion with the ED doctor, fill out baseline measures, including expectations of recovery, and then be randomly allocated to pregabalin plus evidence-based advice or placebo plus evidence-based advice.

If participants present at times when no research staff are in attendance, they will be asked by an ED doctor or nurse to provide written consent for the research team to contact them as soon as is practicable. If, when contacted, these patients agree to be involved in the trial, they will be screened at a local GP clinic, provide informed consent after discussion with the GP, and then be randomised and provided with the first medication dose.

After discharge from ED, the trial GP will evaluate all patients via telephone review (3 days after randomisation and then weekly thereafter) to titrate the dose based on the patient’s tolerance and any adverse effects, and to promote retention. Participants will be offered an optional GP visit during the active intervention phase. Participants will also be able to contact the trial GP if they have questions regarding the medication dose or any side effects.

Strategies for reaching target sample size include employing casual staff to monitor EDIS for as much of the 24 hour day as possible, using a permission to contact process for patients arriving in ED when there are no research staff, regularly reminding ED nurses and clinicians about the trial, and maintaining a high profile of the trial in the ED.

### Randomisation

Participants will be randomly allocated to either treatment group. The randomisation codes will be generated by the study statistician using computer-generated random numbers. The statistician will provide a randomisation list in variable block sizes of 4–6 for the whole trial to the study dispensing pharmacy, unavailable to those who enrol participants. To balance potential confounders and to conceal allocation, there will be separate randomisation schedules for each site. The randomisation schedule, containing patient initials, date of birth and randomisation code, will be kept in a sealed envelope in a locked filing cabinet in the pharmacy, and will be accessible after hours in case unblinding is needed.

Study medication will be prepared according to the randomisation schedule by a pharmacist not involved with data collection, then sealed in an opaque medication kit and stored in a locked drug room in the ED or at the General Practice. Allocation will occur immediately following baseline assessment. The doctor or nurse (blinded) will select the next kit in the box, record the participant’s randomisation number and provide the sealed medication kit to the participant (blinded). This will randomise them to one of two groups – pregabalin or placebo – and ensure concealed allocation and blinding of research staff, trial GPs, participants, care providers, outcome assessors and data analysts. Participants will be considered to have entered the study when the kit is opened.

### Study interventions

Using placebo as a comparator will allow us to compare pregabalin plus evidence-based advice with evidence-based advice only. All patients will receive a self-help resource to aid recovery (evidence-based advice), which describes the most effective interventions currently available (reassurance and an active physical regime including exercises) [36], ensuring no patient is without any treatment.

#### Evidence-based advice

On randomisation, an evidence-based advice booklet *Whiplash Injury Recovery: A Self Help Guide (2*^*nd*^*edition*) [36], based on recommendations of the current Australian Guidelines for Whiplash Management, will be given to all patients. It provides information about whiplash, assurance about prognosis, advice to stay active and resume working, information on correct posture and resuming functional daily activities and an exercise program proven to reduce neck pain.

#### Pregabalin or placebo

Pregabalin and placebo identical in size, appearance, smell, taste and weight (Avicel^®^) will be encapsulated by a compounding pharmacy to ensure blinding of research staff, participants, ED staff and trial GPs.

##### Dose titration

Patients will receive one pregabalin capsule (75 mg) or one placebo capsule orally twice daily starting immediately on randomisation. Figure 2 delineates the dose escalation/reduction/modification regimen, which is standard clinical practice, and has also been used in previous pregabalin trials [37, 38].

**Fig. 2 Fig2:**
[figure not shown]
Dosing algorithm for pregabalin/placebo

##### Rationale for duration of treatment

There are no firm guidelines on treatment duration. Surgical studies have used pregabalin for 10 days to 2 weeks post-operatively [30]. For chronic neuropathic pain, 2–4 weeks of treatment is recommended [39]. In a recent trial, patients with sciatica were treated for up to 8 weeks [25]. To avoid missing benefit we will give 28 days of treatment before weaning.

### Concomitant medications

Participants will be asked not to seek other treatments and where possible not to change current medications, and GPs will be asked within reason to refrain from referring or suggesting additional or alternative treatments. All participants will maintain diaries in which they will record information about other treatments and medication taken. During the trial, GP’s calls to patients, all medications and doses will be recorded, including prescription and over-the-counter medications and natural health products, to be included in the analysis. At the end of 5 weeks, participants will be permitted to seek further treatment (e.g. additional medication, physiotherapy, etc.) if required, information about which will be recorded in cost diaries during follow-up.

### Breakthrough medication

Participants who experience high levels of continuing or worsening pain will be able to return for review by the trial GP. If there is debilitating continuing and worsening pain or continuing high levels of pain that have not improved after 7 days of treatment, despite following the trial regimen, rescue medication (Paracetamol 1000 mg qid prn or oxycodone 5 mg prn if paracetamol is not sufficient) will be provided by the trial GP. These medications are consistent with current clinical practice guidelines for WAD management [8]. Ancillary and post-trial care will be provided by the patient’s GP.

### Adherence to study medication

Adherence will be assessed by (1) daily self-recorded medication intake, (2) counts of returned tablets following treatment completion and (3) the trial GP will ask about adherence during telephone-based reviews starting at 3 days post randomisation. Adherence will be encouraged during weekly phone calls to participants. There will be full accountability for all drugs given to patients.

### Study outcome measures

Primary outcomeAverage neck pain intensity over the last 24 hours at 3 months post randomisation measured using the Numeric Pain Rating Scale (NRS) [40] of 0–10.Secondary outcomes: feasibilityProportion of screened patients eligibleProportion of eligible patients enrolledEnrolment rate (i.e. number of enrolments per month per site)Protocol complianceLogistic model for recruitment to a full trial, including staffing requirements, and strategies to overcome any barriers identified, for example, recruiting through GP practices using the ‘permission to contact’ system for patients who have presented to ED, if recruitment is easier than through EDs directlyFeedback from ED clinicians, local GPs, trial GPs and patients on their experience with the trial and areas for improvement, to inform a full scale trialSecondary outcomes: clinicalNeck pain intensity (NRS 24 hours) at 5-week and 6- and 12-month follow-ups post randomisationNeck Disability Index (NDI) [41] at 5 weeks, 3, 6 and 12 months to measure disabilityPain Catastrophising Scale (PCS) [42] at 5 weeks, 3, 6 and 12 months to measure pain catastrophisingPost-traumatic Stress Diagnostic Scale (PDS) symptom score [43] at 5 weeks, 3, 6 and 12 months to measure post-traumatic stress symptomsDepression, Anxiety and Stress Scale (DASS) [44] at 5 weeks, 3, 6 and 12 monthsGeneric measure of health status scores (SF-12) [45] at 5 weeks, 3, 6 and 12 monthsProportion of patients who lodge a compensation claim at 5 weeks, 3, 6 and 12 monthsNumber of doses of breakthrough medication taken measured at 5 weeks, 3, 6 and 12 monthsNumber of adverse events compared between treatment groupsS-LANSS [46] during follow-up from baseline, compared between treatment groups

Outcome measures have established reliability and validity, are recommended by the International Whiplash Summit [14] and the Bone and Joint Decade Neck Pain Task Force [47], and follow IMMPACT recommendations for design of clinical trials for chronic pain prevention [48].

The Recommendations for Interventional Trials (SPIRIT) figure demonstrates the timing of the interventions and outcomes (Fig. 3).

**Fig. 3 Fig3:**
[figure not shown]
SPIRIT diagram

### Sample size

Since this is a feasibility study, a sample size calculation was not performed. We will aim for 30 participants (15 in each arm) as this will be a large enough sample to inform about the practicalities of delivering the intervention in the ED, recruitment, uptake and attrition. The results of this study will inform any necessary post-trial modifications or remodelling prior to implementation of a larger scale multisite RCT.

### Loss to follow-up

This feasibility study aims to assess attrition rates for a future large RCT. In order to reduce attrition, we will aim to foster trusting relationships via weekly telephone calls to help participants feel engaged in the study. This will also improve adherence to intervention protocols. If participants discontinue or deviate from intervention protocols, we will attempt to collect at least the primary outcome.

### Unblinding

The Principal Investigator will be able to unblind individual cases if any of the following criteria are met:Emergency unblinding – to make a clinical treatment decision or when an unexpected serious adverse event occursAt the request of the Data Safety Monitoring BoardAt the conclusion of the study to determine the potential effect of intervention

If a medically qualified investigator requires identification of the trial medication composition, they must quote the randomisation code, participant initials and date of birth to the Principal Investigator, who will contact the pharmacy and quote the randomisation code and trial title. The pharmacy will unblind for the specific participant only. The medically qualified investigator will talk to and unblind the participant.

### Data management

This trial will be conducted in accordance with ICH Guidelines for Good Clinical Research Practice [49] and relevant local ethical regulations. Study data will be collected and managed using a regulatory approved electronic data capture system (REDCap) hosted at UQ [50], on the UQ server. REDCap is a secure, web-based application designed to support data capture for research studies, that will house all clinical and safety data. It will provide (1) an intuitive interface for validated data entry; (2) audit trails for tracking data manipulation and export procedures; (3) automated export procedures for seamless data downloads to common statistical packages; and (4) procedures for importing data from external sources.

Data from follow-up questionnaires will be entered by patients via email links to the REDCap database, and the remaining data by the research team. Data quality will be assured through range checks for data values. Integrity of trial data will be monitored by regularly scrutinising data for omissions and errors. In order to protect confidentiality before, during and after the trial, personal information about potential and enrolled participants will remain secure in a locked research office at GCUH or Ipswich Hospital. Study data will be retained, securely password protected, for a minimum of 15 years from completion. Details of data management procedures can be found in the protocol.

### Data analyses

Because of participant numbers and the aims of the study, we will report descriptive analyses. Recruitment rate (number of patients approached, number consenting to participate and number eligible to be randomised) will be reported, as will frequencies and proportions of missing data and participant attrition, both during intervention and follow-up periods.

A model for recruitment to the main trial will be described, including the success of various recruitment strategies, for example, is recruitment easier though EDs or through GP practices using the ‘permission to contact’ system? It will also include how the ED and general practice sites worked together, how to maximise research staffing efficiency in terms of rostering, etc. Relevant factors that could create barriers to subsequent study completion will be described, and strategies to overcome these discussed.

#### Statistical analysis

Trends in the data will be analysed by our biostatistician blinded to group allocation using intention-to-treat. We will analyse the effect of treatment separately for each outcome using mixed-effects models with random intercepts for individuals to account for correlation of repeated measures within participants. Treatment group will be included as a fixed effect. We will obtain estimates of the effect of the intervention and 95% confidence intervals by constructing linear contrasts to compare the adjusted mean change (continuous variables) or difference in proportions (dichotomous variables) in outcome from baseline to each time point between the pregabalin plus evidence-based advice and placebo plus evidence-based advice groups. Missing data will be examined for patterns of missingness.

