### Participants

#### Inclusion criteria

Individuals with Grade II WAD and within 48 hours of injuryCurrently experiencing at least moderate pain (visual analogue scale: ≥ 5/10)Aged 18–65 yearsProficient in written and spoken English

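### The random-intercept model with change-from-baseline contrasts gives baseline pain the same variance and correlation as follow-up pain, so the 95% CI for the 3-month effect is probably somewhat too narrow

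*Protocol article*

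**What the plan says.** The protocol article, Statistical analysis, fixes the random part of the model and one term of the fixed part: "mixed-effects models with random intercepts for individuals to account for correlation of repeated measures within participants. Treatment group will be included as a fixed effect". It names no other fixed term. The effect is to be obtained "by constructing linear contrasts to compare the adjusted mean change (continuous variables"), taken "in outcome from baseline to each time point between the pregabalin plus evidence-based advice and placebo plus evidence-based advice groups". The output is described as follows: "We will obtain estimates of the effect of the intervention and 95% confidence intervals".

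Four other places bear on this:
- Design overview gives five measurement times: baseline, 5 weeks, and 3, 6 and 12 months.
- Inclusion criteria require "at least moderate pain (visual analogue scale" score of 5/10 or more). The Abstract gives the same threshold on the NRS.
- Randomisation says "there will be separate randomisation schedules for each site".
- The Abstract says the 3-month primary outcome will be compared by analysis of variance, with no mention of a mixed model.

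**The concern.** If change from baseline is a contrast within the mixed model, baseline has to be one of the five responses. A random intercept with a single residual variance then forces compound symmetry: one variance at all five visits and one correlation for all ten pairs of visits.

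The trial's own design makes that doubtful. Baseline pain is selected to be high, while follow-up pain can fall anywhere from 0 to 10. The Background expects a mixture of people who recover and people who stay disabled, which tends to spread the later scores. A score taken within 48 hours of injury is also likely to correlate less with month 3 than the later visits do with one another.

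If so, the model borrows its error variance from the more tightly correlated follow-up pairs and understates the variance of the baseline-to-3-month change. The interval is then too narrow. That matters because Specific objectives lists estimating potential effectiveness in order to size the definitive trial, and because the interval is the main guard against over-reading an estimate from 15 patients per arm.

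**Working it through.** The article states no SD for follow-up pain, no correlation, no power and no sample size calculation, so there is no figure of its own to reproduce.

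**Inputs from the article.** 15 per arm; five visits; entry pain at least 5/10; acute ED pain of 6.2 with SD 1.5 in the investigators' other trials (Limitations).

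**Assumptions.** Follow-up SDs of 2.0–3.0; baseline to follow-up correlation r0 of 0.1–0.5; follow-up to follow-up correlation rf of 0.6–0.8; no dropout; time and treatment-by-time included in the model.

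**Closed form.** Under compound symmetry the residual variance is the mean variance minus the mean covariance, and the model variance of a change is twice that. The true variance of the 3-month change is SD0² + SD3² − 2·r0·SD0·SD3.

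*Base case:* SDs 1.5, 2.3, 2.5, 2.5, 2.5; r0 = 0.3; rf = 0.7.
- Mean variance: (2.25 + 5.29 + 3 × 6.25)/5 = 5.258.
- Mean covariance: [0.3 × 1.5 × (2.3 + 7.5) + 0.7 × (3 × 2.3 × 2.5 + 3 × 2.5 × 2.5)]/10 = (4.41 + 25.20)/10 = 2.961.
- Residual variance: 5.258 − 2.961 = 2.297. Model variance of change: 4.594.
- True variance of change: 2.25 + 6.25 − 2 × 0.3 × 1.5 × 2.5 = 6.25.
- SE ratio: √(4.594/6.25) = 0.857. In NRS points the SE is √(2 × 4.594/15) = 0.78 against √(2 × 6.25/15) = 0.91.
- Approximate coverage with 28 × 4 = 112 degrees of freedom: P(|Z| ≤ 1.981 × 0.857) = 91.1%. Simulation of this case gave 90.8% (30,000 trials).

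*Milder case:* follow-up SD 2.0, r0 = 0.4, rf = 0.6. Model variance 2 × (3.65 − 1.92) = 3.46; true variance 2.25 + 4 − 2.4 = 3.85; SE ratio 0.95; coverage about 94%.

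*Mildest case:* follow-up SD 2.0, r0 = 0.5, rf = 0.6. Model variance 2 × (3.65 − 2.04) = 3.22; true variance 2.25 + 4 − 3 = 3.25; SE ratio 0.995; coverage about 95%.

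**Simulation with the entry rule imposed.** Baseline was drawn with mean 6.2 and SD 1.5, then truncated at 5. Scores were clipped to 0–10, with 6,000 null trials per row. Correlations are those before truncation. Widths are mean 95% CI widths in NRS points.

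| Follow-up SD | r0 | rf | Coverage, random intercept | Coverage, ANCOVA | Width, random intercept | Width, t-interval on change | Width, ANCOVA |
|---|---|---|---|---|---|---|---|
| 2.5 at all visits, no truncation | 0.7 | 0.7 | 94.9% | 94.9% | 2.65 | 2.74 | 2.55 |
| 2.5 | 0.3 | 0.7 | 91.2% | 94.5% | 2.96 | 3.44 | 3.39 |
| 2.0 | 0.3 | 0.6 | 93.8% | 95.4% | 2.66 | 2.94 | 2.81 |
| 2.5 | 0.1 | 0.8 | 88.1% | 95.4% | 2.84 | 3.72 | 3.51 |
| 2.5 | 0.5 | 0.7 | 93.3% | 95.1% | 2.82 | 3.09 | 3.14 |
| 3.0 | 0.2 | 0.8 | 88.0% | 95.0% | 3.17 | 4.05 | 3.99 |
| 2.5, with 1-point site effect | 0.3 | 0.7 | 92.0% | 95.2% | 2.98 | 3.50 | 3.46 |

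The first row isolates the cause: when variances and correlations really are equal, the random-intercept interval is correct. The last row shows that leaving out a balanced site effect does not lower coverage.

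**Precision.** In the base case, adjusting for baseline gives variance 6.25 × (1 − 0.3²) = 5.69, which is 9% below the change score. With truncation the gain is smaller: ANCOVA intervals run from about 6% narrower to about 1% wider than the t-interval on change. The main benefit is correct coverage, with precision a lesser one.

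**The case against.** **The sizes are assumed.** The follow-up SDs and correlations appear nowhere in the article. The SD of 1.5 comes from other trials and is not described as truncated. Entry is judged on current pain, whereas the outcome is average neck pain over 24 hours, so the outcome's baseline is restricted indirectly and not cut exactly at 5. All of this stands. It means the shortfall is a range that can shrink to nothing.

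**The study is descriptive and small.** It disclaims evidence of effectiveness, is not powered for these effects, and attaches no test or progression rule to the interval. Even valid intervals are about 2.8–4.0 points wide. This stands as a reason for moderate weight. It does not remove the point, because the estimate has a stated use in sizing the full trial.

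**A condensed article may leave details to the full plan.** This is fair for the list of fixed effects, but not for the random structure, which the article states.

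Three stronger readings are tempting, and the article does not support them:
- *Treatment is the sole fixed effect, so contrasts by visit cannot be obtained.* A treatment-only model would indeed return a time-averaged difference: 0.8 of a constant follow-up effect, since one of five visits carries none. But the text says only that treatment is included, and contrasts at each time point imply time and treatment-by-time. The list is incomplete, and that does not make the model unworkable.
- *Leaving out site invalidates the intervals.* Site is not named, but it is not excluded either, and coverage was 92.0% with a site effect against 91.2% without.
- *The intervals are unusable.* A loss of about 1 to 7 percentage points, conditional on assumptions, is miscalibration of mild to moderate size.

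**Conclusion.** The concern holds as a moderate one. The article commits to random intercepts only and to change from baseline as a model contrast. In a trial that selects on high entry pain, that combination probably understates the standard error of the 3-month effect. Under the unequal-variance scenarios examined, coverage is about 88–94% in place of 95%. With follow-up SD 2.0 and correlations of 0.5 and 0.6 there is no material loss. The result depends on the assumed follow-up SDs and correlations, complete data, and baseline being analysed as a response.

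A conditional consequence follows for planning. If the model-based variance of change were carried into the full trial's sample size, the base case would give 4.594/6.25 = 0.735 of the required number, about 27% too few. A planner who used the observed 3-month SD would not make that error.

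Separately, no covariate is named for the adjusted mean change, and the Abstract describes a different method for the same outcome. A reader cannot tell which analysis yields the reported effect.

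**What to change.** For neck pain intensity, replace the model description with the following:
- Responses: NRS scores at 5 weeks and 3, 6 and 12 months. Baseline is not a response.
- Fixed effects: treatment, time, treatment-by-time, baseline pain and site. Site is included for consistency with the separate schedules by site and for precision; its absence does not invalidate the interval.
- Covariance: unstructured, with a heterogeneous-variance structure as the pre-stated fallback, and small-sample degrees of freedom such as Kenward-Roger.
- Reported effect: the treatment contrast at 3 months with its 95% CI.

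An ANCOVA of the 3-month score on baseline is an acceptable simpler alternative. Whichever is chosen, state what the adjustment consists of and make the Abstract agree with it.

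The cost is wording only, since baseline pain and site are already collected. An unstructured covariance for four visits has 10 parameters, which is a real burden at 30 patients before attrition; hence the fallback. The interval will usually be wider than under the present model: in the central simulated scenario 3.39 against 2.96 NRS points, about 15%. That extra width corrects the understated error.
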